**Fig. 1 Fig1:**
[figure not shown]
Study design flow chart. PLW, Parent-Led Weaning; BLISS, Baby-Led Introduction to SolidS. Adapted from Daniels et al. (2015) [18]

This study has been approved by Hospital de Clínicas de Porto Alegre (HCPA) Ethics Committee (under number 2019-0230, CAAE: 1537018500005327) and is currently registered in the Brazilian Clinical Trials Registry (ReBEC) with accession number RBR- 229SCM. The protocol was written according to SPIRIT guideline, and its checklist was carried out (Additional File).

Written informed consent will be obtained from all responsible of the participants before randomization. This document specifies all steps carried out in the research, as well as the consent to publish the data and the confidentiality, making it clear that the results will be presented together, without identifying or naming the participants. The research team will clarify all participants’ questions about the research procedures before signing the consent form. The research will bring direct benefits of nutritional support to participant children, as well as clarify any doubts expressed by mothers at the start of the study and throughout the study period, until age 12 months. A survey will provide feedback on nutrition assessment results and laboratory tests, by e-mail or letter; in case of relevant changes, a copy will be forwarded to the referral health unit. If any nutritional deficit or excess is detected, the child will be referred to an appropriate health care provider.

### Participants and recruitment

Participants will consist of parents and their lactating children. Recruitment will take place by online invitation, through social networking pages, targeted mothers’ groups, and the HCPA bulletin board. The invitation letter will contain a phone number and an email address where parents can leave a message if they wish to participate. Once checked against the inclusion criteria, those found eligible will receive a standardized message explaining the study details, risks, and benefits, and any further questions will be answered by the researchers by phone or e-mail. After confirmation of interest, the consent form will be sent by email. Once the signed consent form is received back, the participant will be randomized to one of the groups.

### Inclusion criteria

Mothers living in Porto Alegre, Rio Grande do Sul, Brazil (population 1,483,771) [61] or nearby cities, with healthy singleton infants born at term, with birth weight ≥ 3500 g, between 0 and 4 months of life and who have not yet started the CF process will be eligible to participate.

### Exclusion criteria

Children who develop neurological deficits or congenital abnormalities, or any food restriction (as indicated by their pediatrician) during the follow-up period will be excluded from the study.

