**Methods/design:**

To evaluate and compare three different complementary feeding methods. Data on 144 mother-child pairs will be randomized into intervention groups by methods: (A) strict Parent-Led Weaning; (B) strict Baby-Led Introduction to SolidS; and (C) a mixed method. Prospective participants from Porto Alegre, Brazil, and nearby cities will be recruited through the Internet. The interventions will be performed by nutritionists and speech therapists, at 5.5 months of age of the child, at a private nutrition office equipped with a test kitchen where meals will be prepared according to the randomized method. The pairs will be followed up at 7, 9, and 12 months of age. Data will be collected through questionnaires designed especially for this study, which will include a 24h child food recall, questionnaires on the child’s and parents’ eating behavior, oral habits, eating difficulties, and choking prevalence. At 12 months of age, children will undergo blood collection to measure hemoglobin, ferritin, and C-reactive protein, saliva collection for analysis of genetic polymorphisms, and oral examination. Anthropometric parameters (child and maternal) will be measured at the baseline intervention, at a 9 month home visit, and at the end-of-study visit at the hospital. The primary outcome will be child growth and nutritional status *z*-scores at 12 months; secondary outcomes will include iron status, feeding behavior, acceptability of the methods, dietary variety, choking, eating behaviors, food preferences, acceptance of bitter and sweet flavors, suction, oral habits, oral hygiene behavior, dental caries, gingival health status, and functional constipation.

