### Adherence

To ensure the families follow these instructions, a blinded researcher will conduct a phone call when the child is 7 months of age and ask some key questions (about food consistency when the child started to eat, and at 7 months; if the child takes food to mouth alone; and if the child receives food in spoon). A different researcher will analyze the answers and compare them with further data collected at the 9-month visit, in addition to a 24-h dietary record. These records will be collected during the home visit, by trained researchers. However, as some mothers might not be able to quantify food intake exactly, all participants will also be asked when they introduced a variety of different foods at the 9-month and 12-month visits. Questionnaires to assess adherence to self-feeding, breastfeeding practices, and introduction of complementary foods at 6 months will also be administered at the 9-month and 12-month visits. The rates of adherence will be analyzed. All participants will be included to the final analyses, regardless of having followed the method, since the analyzes will be made by intention-to-treat.

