### Outcome measures

*Z*-scores of anthropometric measurements (weight for age, weight for length, length for age, and BMI for age *z*-scores) will be our primary outcome measure to investigate child growth and nutritional status. As secondary outcomes, we will analyze choking prevalence, dietary variety, food and flavor preference, child and parent feeding behavior, iron deficiency, oral hygiene behavior, dental caries, dental development, gingival health status, the prevalence of functional constipation, maternal perception of the CF methods, and prevalence of child eating disorders.

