### Statistical analysis

The database will be prepared in SPSS (Statistical Package for the Social Sciences) version 21.0, with double entry and validation. Descriptive analyses of continuous and categorical variables will be performed, in the isolated 10% quality assurance sample and in the total sample. Parametric data will be expressed as mean ± standard deviation. All analyses will be conducted by the intention-to-treat principle. The primary analysis will determine whether PLW, BLISS, or the mixed method results in differences in child growth *z*-scores at 12 months of age. Regression analyses will be used to analyze secondary outcomes, including iron intake and status. We will consider adjusting plasma ferritin where there is evidence of infection or inflammation, as indicated by elevated CRP. Statistical significance will be accepted at *p* < 0.05.

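### Excluding children who develop a food restriction or other condition during follow-up contradicts the stated intention-to-treat analysis and leaves room for bias of unknown direction and size

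*Protocol article*

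**What the plan says.** All references are to the protocol article.

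- **Entry.** Infants are eligible "between 0 and 4 months of life and who have not yet started the CF process" (Inclusion criteria).
- **Randomisation.** "Once the signed consent form is received back, the participant will be randomized to one of the groups" (Participants and recruitment).
- **Follow-up.** "The pairs will be followed up at 7, 9, and 12 months of age" (Abstract, Methods/design).
- **Exclusion.** The criterion names a neurological deficit and a congenital abnormality that appear after entry, and then adds this clause: "or any food restriction (as indicated by their pediatrician) during the follow-up period will be excluded from the study" (Exclusion criteria).
- **Analysis set.** "All participants will be included to the final analyses, regardless of having followed the method, since the analyzes will be made by intention-to-treat" (Adherence). The Statistical analysis section repeats the rule without qualification: "All analyses will be conducted by the intention-to-treat principle".
- **Outcomes touched.** The anthropometric z-scores "will be our primary outcome measure to investigate child growth and nutritional status" (Outcome measures). For iron: "Regression analyses will be used to analyze secondary outcomes, including iron intake and status" (Statistical analysis).

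No section says that a child excluded under this criterion continues to be measured or stays in the analysis.

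**The concern.** An exclusion triggered by something that happens during follow-up acts on children who already belong to a randomised group. If the trigger is related to the allocated method and also to the outcome, the children who remain are no longer comparable across arms.

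Neurological deficits and congenital abnormalities are a minor worry here. Neither has an evident link to how solids are introduced, and a congenital abnormality precedes randomisation even if it is recognised later. The food-restriction clause is different. It is broad and undefined, it can apply once foods have been introduced by the allocated method, and a restricted diet can bear on growth and iron intake. Mothers know their group from the first intervention at 5.5 months (Randomization; Study groups), and the paediatrician who indicates the restriction is not described as blinded.

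Two things are at stake: whether the primary comparison of 12-month z-scores is of the groups as randomised, and whether the analysis set is fixed. As written, a team could keep or drop such a child and cite the protocol for either choice.

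**Working it through.** **Step 1: timing.** Randomisation follows return of the consent form, in infants aged 0 to 4 months who have not started solids. The exclusion applies to conditions that develop during follow-up, with contacts at 7, 9 and 12 months. The wording cannot be read as a baseline criterion.

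**Step 2: consequence.** The stated consequence is exclusion from the study, not a stop to the feeding method. Taken literally, a child excluded at 8 months has no 12-month z-score and no 12-month blood sample, yet the other two sections require that child in the final analyses.

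**Step 3: illustration of bias.** The documents give no exclusion rates and no outcomes for such children, so every input here is assumed. Let p be the share excluded in an arm and D the distance, in SD, by which excluded children lie below their arm's mean. With no true difference, the retained mean rises by p·D/(1 − p), so the spurious difference between arms B and A is

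bias = p_B·D/(1 − p_B) − p_A·D/(1 − p_A).

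| Excluded A / B | D = 0.5 | D = 1.0 |
|---|---|---|
| 5% / 5% | 0 | 0 |
| 2% / 8% | 0.033 | 0.067 |
| 5% / 10% | 0.029 | 0.058 |
| 5% / 15% | 0.062 | 0.124 |

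Example, last cell: arm B rises by 0.15/0.85 = 0.1765 and arm A by 0.05/0.95 = 0.0526; the difference is 0.124.

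If the gap is instead measured between retained and excluded children, the shift is p × gap. For 15% against 5% and a gap of 1.0, the bias is 0.10 × 1.0 = 0.10. For 10% against 3% and a gap of 0.7, it is 0.07 × 0.7 = 0.049.

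Equal rates give zero only if the excluded children are alike. With 5% in each arm but D = 1.0 in one and D = 0.5 in the other, the bias is 0.0526 × 0.5 = 0.026. If excluded children lie above their arm's mean, the signs reverse.

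**Step 4: precision.** The plan's only design figure is 48 per group (144 in total), for 80% power at 5% with SD 1. For half an SD, two-sided, the normal approximation n = 2 × (z_a + z_b)² / d², with z_a = 1.960, z_b = 0.842 and d = 0.5, gives 63 per group, so 48 is not reproduced. That is a separate matter, and this point does not depend on it. Taking n = 48 as given, power for d = 0.5 is Φ(d × √(n/2) − z_a) = 68.8%. It falls to 66.6%, 64.2% and 61.7% if 5%, 10% or 15% of each arm is excluded.

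**The case against.** The strongest reply is that the criterion covers a narrow set of medical events in healthy term infants, that few will occur, and that nothing shows they will differ by arm. All arms receive the same advice on meal timing, foods to avoid, and iron and energy; they differ mainly in food consistency and adult participation. A restriction prompted by a particular food has no obvious reason to cluster in one arm. The Adherence wording can also be read as covering only non-adherence, and a full protocol or SAP might define the analysis set.

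Much of this stands as a limit on size. It does not remove the contradiction: the Statistical analysis section applies intention-to-treat to all analyses without qualification, and the exclusion rule is a stated rule, not a missing detail.

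Three stronger readings are tempting, and the documents do not support them.

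- A reader might infer that the rule hides harm because the excluded children are those growing poorly. The direction is not derivable. The protocol refers children with a nutritional deficit or excess to a health care provider (Study design); if a restriction followed, it could concern either.
- A reader might infer that children are excluded for choking or growth faltering. The criterion names neither, and the Adverse events section monitors both.
- A reader might infer that the restriction is decided by someone who knows the allocation. The documents do not say whether the paediatrician knows it, and mothers do not know it before the first intervention.

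**Conclusion.** The contradiction holds with high confidence. The Exclusion criteria section, followed as written, makes a post-randomisation exclusion, while the Adherence and Statistical analysis sections promise that all participants are analysed by intention-to-treat.

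The bias is possible, not demonstrated. It requires the rate or the type of excluded child to differ by arm, and the food-restriction clause is the plausible route. On assumed inputs the spurious difference is 0 with equal exclusion of similar children and about 0.03 to 0.12 SD with unequal exclusion, reaching 0.05 to 0.12 SD in the clearly unequal cases. The top of that range is about a quarter of the half-SD design difference (0.124/0.5 = 0.25). These figures show scale only and are not estimates for this trial. The conflict should be settled before analysis because the rule determines which children contribute to the primary outcome.

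**What to change.** Reconcile the three sections:

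1. Apply these conditions as exclusions only before randomisation.
2. Replace the follow-up exclusion with wording such as: *Children who develop one of these conditions after randomisation remain in the study, are measured at 9 and 12 months where the family agrees, and are analysed in their randomised group; any departure from the allocated method is recorded as non-adherence.*
3. Report the number, type and timing of these events by arm.
4. Give the analysis without these children as a sensitivity analysis.

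The cost is a short amendment and a few continued follow-up visits. Clinical care of the child is unaffected, since the change concerns only measurement and analysis. Keeping children who have left their method dilutes the contrast slightly, which intention-to-treat already accepts.

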### Sample size

The sample size was calculated using WinPepi® software version 11.65, based on previously published studies on the subject. Considering a unit standard deviation of 1, statistical power of 80%, and a significance level of 5% to detect a difference in BMI of 0.8 kg/m^2^ [18, 24], the sample calculation for a half standard deviation difference will consist of 48 mother-infant pairs for each of the three intervention groups, totaling 144 pairs of mothers and infants.

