## Methods/design

### Study design

The study will consist of a three-arm controlled trial (Fig. 1), which will intend to randomize mothers and their respective infants into three different groups of CF: (A) strict Parent-Led Weaning (PLW), which is the control arm; (B) strict Baby-Led Introduction to SolidS (BLISS); and (C) mixed method: a combination of PLW and BLISS created especially for this study. Three interventions will be performed throughout the study, and measurement of the main outcomes is expected at 12 months of age. The framework expected to the outcomes is that BLISS and mixed methods will be superior to the PLW method.

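### The stated 80% power for half an SD with 48 pairs per arm does not hold for a comparison among three separate methods: each two-sided pairwise contrast has about 68%

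*Protocol article*

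**What the plan says.** The sample size section of the protocol article gives all its inputs in one sentence. It opens with "Considering a unit standard deviation of 1, statistical power of 80%, and a significance level of 5" per cent, sets the target as "to detect a difference in BMI of 0.8 kg/m^2", and concludes that "the sample calculation for a half standard deviation difference will consist of 48 mother-infant pairs for each of the three intervention groups", 144 pairs in all. It gives neither the sidedness of the test nor which arms are compared.

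Three other places bear on the reading:
- Study design names Parent-Led Weaning (PLW) as the control arm and expects that "BLISS and mixed methods will be superior to the PLW method".
- Outcome measures makes the primary outcome a set of growth z-scores, with BMI-for-age among them.
- Statistical analysis asks whether the three methods lead to different growth z-scores at 12 months, with significance at p < 0.05. It names the methods separately.

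**The concern.** A reader who puts the stated inputs into the usual two-group formula does not get 48. Half an SD needs more pairs per arm than that, and 0.8 SD needs far fewer. The sentence also offers two effect sizes, 0.8 kg/m² and half an SD, which differ if the SD of 1 is in kg/m².

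Growth faltering is one of the questions that motivate the trial. If BLISS and PLW do not differ significantly in growth, readers will take that as the result of a study with 80% power for half an SD. If the contrast has about 68%, the chance of missing such a difference is about 32%, not 20%, and the null result reassures less than the text implies.

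**Working it through.** **Inputs from the sample size section:** SD 1, power 80%, significance level 5%, effect 0.5 SD (also given as 0.8 kg/m²), 48 per arm, 3 × 48 = 144. Sidedness and comparison are not stated, so each plausible choice is tried. Losses are set to zero until the last step.

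**Formula.** For two groups with n in the smaller and r·n in the larger, n = (1 + 1/r)(z₁₋α + z₀.₈₀)² / d², with z₁₋α/₂ in place of z₁₋α for a two-sided test. Two-sided 5%: (1.960 + 0.842)² = 7.849. One-sided 5%: (1.645 + 0.842)² = 6.183. Results from the noncentral t follow each normal approximation.

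**1. Reproducing 48.** Take PLW against BLISS and mixed pooled, r = 2, two-sided, d = 0.5: n = 1.5 × 7.849 / 0.25 = 47.1 (t-test 47.7). That is 48 in PLW and 96 in the pooled group, 144 in total, an exact match. Power at 48 versus 96 is 80.2%.

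**2. Any two arms, two-sided, d = 0.5.** n = 2 × 7.849 / 0.25 = 62.8 (t-test 63.8, so 64 per arm). Power at 48 per arm: Φ(0.5 × √24 − 1.960) = Φ(0.489) = 68.8% (t-test 67.9%). Difference detectable with 80% power: √7.849 × √(2/48) = 0.572 SD (t-test 0.578).

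**3. Any two arms, one-sided, d = 0.5.** n = 2 × 6.183 / 0.25 = 49.5 (t-test 50.2, so 51 per arm). Power at 48 per arm: 79.0% (t-test 78.4%).

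**4. Three-group F-test, N = 144, largest difference 0.5 SD.**
- One arm 0.5 SD away from the other two: f = 0.5 × √2 / 3 = 0.236, power 70.8%, about 59 per arm needed.
- Third mean midway between the others: f = 0.5 / √6 = 0.204, power 57.4%, about 79 per arm needed.

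**5. The two effect sizes.** If the SD of 1 is in kg/m², 0.8 / 1 = 0.8 SD. Two-sided pairwise, n = 2 × 7.849 / 0.64 = 24.5 (t-test 25.5, so 26 per arm), and 48 per arm would give 97% power. For 0.8 kg/m² to be half an SD, the BMI SD must be 0.8 / 0.5 = 1.6 kg/m². The section does not give that value, and a pairwise test would still need 64 per arm with it.

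**Power at 48 per arm for 0.5 SD, before losses**

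| Comparison | Power |
|---|---|
| Two-sided, PLW vs pooled (48 vs 96) | 80.2% |
| One-sided, pairwise | 78.4% |
| Three-group F-test | 57–71% |
| Two-sided, pairwise | 67.9% |

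**6. Losses (assumed; the article gives no rate).** With 10% loss, 43 per arm: 63% pairwise two-sided, and 76% pooled (43 vs 86). With 20% loss, 38 per arm: 58% and 70%.

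**The case against.** The strongest reply is that the sample size section fixes neither the comparison nor the sidedness, so a shortfall appears only after the reviewer supplies both. One conventional calculation on the stated inputs returns 48 and 144 exactly: PLW against the other two arms together. The superiority expectation in the study design section is compatible with that contrast. A one-sided pairwise test also comes close to the stated power.

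This stands in part. A reader might infer that 48 per arm cannot give 80% power for half an SD under any analysis, and the documents do not support that. But the match does not rescue the text either. The protocol nowhere describes pooling BLISS with the mixed method, or a one-sided test, and the statistical analysis section treats the methods as three. If pooling was the basis, the calculation answers a different question from the stated primary analysis, and BLISS versus PLW still has about 68%.

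On the inputs, a reader might infer that 0.8 kg/m², an SD of 1 and half an SD cannot all be true. They can, if the unit SD is the standardised scale and the BMI SD is 1.6 kg/m². That value may lie in the cited sources, which are not at hand. The fair statement is that the sentence is inconsistent as written and lacks the SD that would reconcile it.

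A condensed article may also leave the allowance for losses to the full protocol, so its absence is not counted as an error here.

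**Conclusion.** The point holds in conditional form. For the comparison among three separate methods that the protocol describes, 48 per arm does not deliver the stated 80% power for half an SD. A two-sided pairwise contrast has about 68% and a three-group F-test 57% to 71%. The claim is met exactly only for a pooled contrast that the protocol does not describe.

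These figures assume equal SDs, a two-sided 5% level with no multiplicity adjustment, no baseline adjustment and no losses. The first two conditions in the effect statement, 0.8 kg/m² and half an SD, agree only through an unstated BMI SD of 1.6 kg/m². How the authors actually reached 48 cannot be settled from the document.

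**What to change.** Keep N = 144 and rewrite the sample size paragraph so that it:
- names the comparison and the sidedness from which 48 was obtained;
- expresses the effect in BMI-for-age z-score units, in line with the primary outcome, or gives the BMI SD that makes 0.8 kg/m² half an SD;
- reports power for each planned contrast: about 68% for 0.5 SD, and 80% for 0.58 SD, for each two-sided pairwise contrast before losses;
- claims 80% for 0.5 SD only if PLW against the other two arms pooled is declared the primary comparison, in which case the statistical analysis section must say so too;
- labels any power after losses as resting on an assumed rate.

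The cost is wording only. No participants are added, but the stated power becomes less favourable.

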### Randomization

After signing the consent form, participants will be sequentially numbered and have their names entered into a randomization list of three blocks and equal numbers, previously computer-generated (http://www.randomization.com) by blinded research staff.

Only at the time of the first intervention will mothers be aware of their group allocation. Assessment data will be collected by a different researcher from the one responsible for the intervention, blinded to the allocation group, in a different room.

